##### Anthropometric measurement and biomarker Indicator

2.4.1.7

Study participants will be assessed on their height (m) and weight (kg) to determine their Body Mass Index (BMI). WHO Anthro software will be used to assess the anthropometric measurement of participants between (15–18 years old) using the BMI for Age metric; the anthropometric measurement of participants between the age of 19 and 35 will be based on WHO standard of underweight if BMI is <18.5 kg/m^2^, normal or healthy weight if BMI is 18.5 kg/m^2^–24.9 kg/m^2^, overweight if BMI is 25–29.9 kg/m^2^, and obese if BMI ≥ 30.0 kg/m^2^ (52). The participants’ skin carotenoid levels will be assessed using the Veggie Meter to assess their fruits and vegetables intake (53).

#### Secondary outcomes

2.4.2

##### WhatsApp engagement

2.4.2.1

The study participants’ engagement will be evaluated using WhatsApp metric indicators, such as the messages read counts, the number of messages replied to, the engagement ratio (this will be engagements requiring replies/responses or actions), the rate of tasks completed, responses to surveys and polls, and the participants’ comments and feedback during the discussion. These metrics are part of the standard metrics used to measure the efficacy of WhatsApp’s use for learning (54, 55). The WhatsApp engagement will be tracked and measured using a combination of manual monitoring and WhatsApp’s inbuilt metrics. Precisely, engagement will be measured using:

Message read receipts (“blue ticks”) to assess content reachTask accomplishment rates, tracked using participants’ interactions (e.g., feedback, photo posting, voice messages) with tasks presentedInteraction frequency, measured by the number of participant-generated responses or queries per module

Additionally, the moderator(s) will be responsible for documenting all engagement in an activity log during the intervention classes and also conduct separate inter-rater reliability checks on a portion of the engagement log. All interactions will be recorded by the moderator in an activity log. These metrics will serve as a proxy for determining participant’s access to and engagement with digital content (56) and will inform the conclusions of the qualitative feedback on the level of WhatsApp engagement in a nutrition intervention program.

##### Knowledge retention

2.4.2.2

Tests using quizzes, polls, Google forms, and self-confidence assessment questions will be used to evaluate the knowledge retention rate of the participants. The tests will focus on the content of the class modules. A Google form knowledge retention assessment questionnaire will be administered, and participants’ audio and video feedback on the intervention modules will be used to assess how the participants have integrated the knowledge gained into their daily activities. This will reflect the effectiveness and efficiency of the intervention program regarding knowledge retention and behavioral change of the participants (57). The integration of these approaches will evaluate the impact on cognitive retention and the real application of knowledge acquired.

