4.	Cultivation and harvesting of IVFs	Teach participants how to grow and harvest IVFs	Introduction to gardening and caring for the plants	Participants will be asked to keep a gardening journal and document the growth and care of their plants
5.	Cultural significance and traditional uses of IVFs	Explore the cultural significance and traditional uses of IVFs	Cultural storytelling and guest speaker session	Participants will be asked to share family traditions or recipes that include IVFs in the group chat
6.	Food safety practices	Understand the importance of food safety and best practices	Introduction to food safety, identifying food safety hazards, and safe handling and preparation of IVFs	Participants will be asked to create a food safety checklist and share same in the group chat
7.	Health benefits and disease prevention	Discuss the health benefits of consuming IVFs nd their role in disease prevention	Health benefits overview and role in disease prevention	Participants will be asked to share personal or family stories where diet changes particularly incorporating IVFs fruits have positively impacted health
8.	Putting it all together: cooking and meal planning	Integrate knowledge to cooking and meal planning with indigenous foods	Cooking techniques, meal planning, and cooking activity	Participants will be asked to implement the meal plan and report back on any challenges
9.	Indigenous foods and sustainability	Understand the role of indigenous foods in sustainable eating practices	Sustainability overview, interactive activity, and group project activity	Participants will be asked to implement a sustainable practice at home and report back any challenges
10.	Review and celebration	Review key concepts and celebrate achievements	Review quiz	Participants will be asked to record (audio) of a reflection of their experience about *Roots and Greens*, include what they have learned and how they have applied it and share it on the group page

**Table 2 tab2:** Study activities and outcome measures according to the stages.

Stage of intervention	Recruitment	Baseline	Intervention period	Post-intervention evaluation
Verbal consent for screening	√			
Eligibility screening	√			
Study invitation	√			
Participants consent		√		
Goal setting for the groups			√	
2-day workshop on gardening activities			√	
Land apportioning for gardening activities			√	
Provision of seeds and farm equipment			√	
Supervision of gardening activities			√	

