### Data analysis

2.5

Descriptive statistics such as frequency and percentages will be used for the socio-demographic characteristics (such as age, gender, student status, and household size) and other outcome of measures (such as knowledge retention, intervention acceptability, and nutrition-related outcomes) that are categorical variables, while mean and standard deviation will be used for the continuous variables. To assess the possibility of bias resulting from missing data, we will conduct sensitivity analyses by carrying out complete case analyses. As opined by Braun and Clarke, this will ensure the robustness and credibility of our result (61). Mixed model analyses will be used to assess the intervention’s impact on skin carotenoid levels, anthropometrics, and diet diversity score (62, 63). The mixed model analysis was chosen because it accounts for repeated measures and can effectively address issues related to missing data. In these analyses, the intervention arms will be treated as the fixed effect so that the measure’s outcome change between the school gardening-only participants and school gardening and nutrition education participants can be assessed by the coefficients or estimated using the least square means. Time and intervention arm will be included as both main effects and interaction effects. The random effect will account for variability variations between groups that might affect the response. We will control for participant’s age, gender, household size, youth status (out-of-school vs. in-school status), community, and state, by including them as covariates in the adjusted models of the mixed model analysis. Mann–Whitney U Test will be used to compare the acceptability of the nutrition intervention between the groups. The analysis will be performed using IBM SPSS (version 23), and the statistical significance will be set at *p*-value <0.05.

As described by Braun and Clarke (61), the participants’ audio (sessions responses) and video recordings (tasks) from WhatsApp engagement will be analyzed using thematic analysis. We will use inductive coding to deduce the theme directly from the data. The convergent mixed method will be used to integrate the qualitative analysis with the quantitative results. This ensures a proper understanding of how participants experienced and engaged with the intervention.

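### Effectiveness and behaviour change are to be inferred partly from participants' recordings, which come from one arm, have no comparator, and are prompted mainly towards learning and application

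*Protocol article*

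**What the plan says.** Section 2.4.2.2 defines knowledge retention as a secondary outcome with several sources. It opens with tests: "Tests using quizzes, polls, Google forms, and self-confidence assessment questions will be used to evaluate the knowledge retention rate of the participants". It then adds a retention questionnaire and participants' recordings, of which it says: "audio and video feedback on the intervention modules will be used to assess how the participants have integrated the knowledge gained into their daily activities". The conclusion drawn from this material is: "This will reflect the effectiveness and efficiency of the intervention program regarding knowledge retention and behavioral change of the participants".

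Section 2.4 and Table 2 place the tracking of knowledge retention within the WhatsApp delivery period.

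Table 1 lists one task per week. Week 10 calls for an audio reflection in which participants are to "include what they have learned and how they have applied it and share it on the group page". Week 7 asks them to "share personal or family stories where diet changes particularly incorporating IVFs fruits have positively impacted health". Week 8 is different: "Participants will be asked to implement the meal plan and report back on any challenges". Week 9 likewise invites challenges after a practice has been tried at home.

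Section 2.5 says that participants' audio responses and "video recordings (tasks) from WhatsApp engagement will be analyzed using thematic analysis", with inductive coding. The themes are then combined with the quantitative results in a convergent mixed-methods design.

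**The concern.** A claim about effectiveness or behaviour change needs evidence that could have come out differently had the programme not worked. That requires a comparison (before and after, or between arms) and a way of asking that leaves room for an unfavourable answer. The recordings have no comparison. The week 10 prompt takes learning and application as given and is answered in front of peers and the course moderators.

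Inductive coding cannot repair this, because it draws its themes from whatever was elicited. At stake is how the results are read. Themes of applied knowledge could be presented as showing behaviour change, or as independent support for the two-arm result, when they partly reflect what participants were asked to say.

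**Working it through.** No arithmetic applies: the point rests on no sample size, error rate or effect size. The check sets the sections against each other.

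1. **What the inference rests on.** Section 2.4.2.2 uses quizzes, polls, self-confidence questions, an online form and recordings. The quizzes and form bear on retained knowledge. The source it names for integration into daily life is the recordings, so the behaviour-change part of the statement leans mainly on them.

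2. **Who supplies them, and when.** Section 2.4 has retention tracked during WhatsApp delivery, and the tracking row of Table 2 is marked only for the intervention period. The gardening-only arm does not receive this delivery. So there is one arm, no baseline and no comparator.

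3. **What the prompts ask.** Count over the ten weekly tasks in Table 1:

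| Feature of the task as printed | Weeks | Count |
|---|---|---|
| Names an audio recording | 10 | 1 of 10 |
| Asks only for accounts of health benefit | 7 | 1 of 10 |
| Invites challenges | 8, 9 | 2 of 10 |
| States sharing with the group | 1, 2, 3, 5, 6, 10 | 6 of 10 |
| Asks about non-use or no change | none | 0 of 10 |

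4. **What the challenge prompts can reveal.** Weeks 8 and 9 first tell participants to carry out an assigned task and then ask about difficulties. They can bring out problems with that exercise. They do not ask whether habits changed or whether the teaching went unused. They soften the lean but do not remove it.

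5. **What else in the plan can carry an effect conclusion.** Table 2 schedules nutrition knowledge and practices, dietary diversity, and anthropometric and biomarker data at baseline and post-intervention. Section 2.5 plans mixed models with an arm-by-time interaction for skin carotenoids, anthropometrics and dietary diversity. That comparison is non-randomised and has limits that section 3.1 acknowledges, but it has the contrast that the recordings lack.

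Taken together, the recordings can describe how participants experienced the course and what they believe they applied. They cannot separate a course that changed behaviour from one that did not.

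**The case against.** The case on the other side is substantial, and much of it stands.

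- **The recordings are not the only evidence.** Section 2.4.2.2 also uses quizzes and a form, and dietary effects are tested between arms. This stands. A reader might infer that the trial's effectiveness conclusion rests on WhatsApp recordings, and the document does not support that.
- **The prompts are not uniformly positive or public.** Weeks 8 and 9 invite challenges, and group sharing is not stated for weeks 4, 7, 8 and 9. A reader might infer that this evidence would look positive even if the education had changed nothing. That is too absolute: unfavourable material can enter, and week 10 is a reflection on experience in which a participant may say that little was applied.
- **Week 7 may be only a teaching exercise.** It names no recording, and nothing says that its stories feed the behaviour-change assessment. This stands, so week 7 matters only if its responses are coded.
- **Table 1 summarises a curriculum that is not shown.** The words put to participants may differ. This is fair, but the printed content of week 10 is specific about what to include and where to post it.
- **Section 2.5 gives a modest purpose for the integration**, namely to understand experience and engagement. This also stands. Nothing there plans to use themes to confirm or rescue a quantitative result. But it leaves section 2.4.2.2 making a larger claim than section 2.5 needs.
- **Negative views have other routes.** The acceptability questionnaire covers burden and opportunity costs, and task completion is tracked under engagement. These help with acceptability and non-response, but they do not ask whether behaviour changed.

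What remains is the inference printed in section 2.4.2.2, set against one-arm recordings and a leading week 10 prompt.

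**Conclusion.** The concern holds in limited form. The recordings lean towards positive accounts and cannot by themselves show effectiveness or behaviour change, so the statement in section 2.4.2.2 goes further than its source allows. No numerical size is given. Any probability of a spurious theme would need an assumed rate of prompted statements, a number of posts and a theme threshold, none of which the plan states or uses.

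The effect is confined to the qualitative part of one secondary outcome, and the between-arm analyses are untouched. The conclusion assumes that Table 1 fairly reflects what participants will be asked and that the week 10 reflection is among the recordings analysed. It is worth correcting because it is cheap and because a leading prompt cannot be put right at analysis.

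**What to change.** 1. In section 2.4.2.2, replace the effectiveness and behaviour-change statement. Say that the recordings describe participants' experience and perceived application. Base conclusions on effectiveness and behaviour change on the two-arm baseline and post-intervention measures, with the themes used to explain those results and not as independent confirmation.
2. Before delivery, word the week 10 prompt neutrally: what, if anything, was new; what, if anything, is now done differently; what was not used, and why. Do the same for week 7 if its responses enter the thematic analysis, asking equally for diet changes that helped, made no difference or did not help.
3. Report accounts that run against the main themes, and the number in the WhatsApp arm who submitted no recording.

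Private submission of the week 10 reflection would reduce pressure from the audience, but it removes a group-sharing moment that is part of the teaching method, so it is optional.

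The cost is one or two prompts and a few sentences, with no added participants, visits or staff. The downside is that the qualitative claim becomes less favourable.

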##### Intervention acceptability

2.4.2.3

The intervention acceptability metric based on the Theoretical Framework of Acceptability (TFA) developed by Sekhon et al. (58) as shown in Figure 4, will be used to determine the acceptability of the nutrition intervention. A questionnaire that captures the seven domains (affective attitude, burden, ethicality, intervention coherence, opportunity costs, perceived effectiveness, and self-efficacy) of acceptability regarding health-related intervention adapted from (59) will be used. The definition of the domains is adapted from Chen et al. (60) is shown in Table 3. Participants’ feedback on the questionnaire on the acceptability of the intervention will be used to determine the acceptability rate of the intervention.

**Figure 4 fig4:**
[figure not shown]
Theoretical framework of acceptability of health-related interventions.

**Table 3 tab3:** Definitions of theoretical framework of acceptability domains.

Domains	Definitions
Affective attitude	Participants feelings about the intervention
Burden	The perceived amount of effort that is required to participate in the intervention
Ethicality	The level at which the intervention fits into the value system of the participants
Intervention coherence	Participants’ comprehension level of the intervention
Opportunity costs	The level of compromises to participate in the intervention
Perceived effectiveness	The efficacy of the intervention
Self-efficacy	Perceived participants’ behavioral capacity

Source: Adapted from (60).

### Data analysis

2.5

Descriptive statistics such as frequency and percentages will be used for the socio-demographic characteristics (such as age, gender, student status, and household size) and other outcome of measures (such as knowledge retention, intervention acceptability, and nutrition-related outcomes) that are categorical variables, while mean and standard deviation will be used for the continuous variables. To assess the possibility of bias resulting from missing data, we will conduct sensitivity analyses by carrying out complete case analyses. As opined by Braun and Clarke, this will ensure the robustness and credibility of our result (61). Mixed model analyses will be used to assess the intervention’s impact on skin carotenoid levels, anthropometrics, and diet diversity score (62, 63). The mixed model analysis was chosen because it accounts for repeated measures and can effectively address issues related to missing data. In these analyses, the intervention arms will be treated as the fixed effect so that the measure’s outcome change between the school gardening-only participants and school gardening and nutrition education participants can be assessed by the coefficients or estimated using the least square means. Time and intervention arm will be included as both main effects and interaction effects. The random effect will account for variability variations between groups that might affect the response. We will control for participant’s age, gender, household size, youth status (out-of-school vs. in-school status), community, and state, by including them as covariates in the adjusted models of the mixed model analysis. Mann–Whitney U Test will be used to compare the acceptability of the nutrition intervention between the groups. The analysis will be performed using IBM SPSS (version 23), and the statistical significance will be set at *p*-value <0.05.

As described by Braun and Clarke (61), the participants’ audio (sessions responses) and video recordings (tasks) from WhatsApp engagement will be analyzed using thematic analysis. We will use inductive coding to deduce the theme directly from the data. The convergent mixed method will be used to integrate the qualitative analysis with the quantitative results. This ensures a proper understanding of how participants experienced and engaged with the intervention.

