#### Sampling technique and sampling size

2.2.1

Our target population consists of unemployed youths, with estimates ranging between 6.8 and 35% (35–38). Since this is a first of its kind study with no prior effect size for power calculation and known prevalence of IVFs consumption among the target population, a conservative sample size calculation approach was used (39). The sample size calculation applied the population proportion of 18.8% (the percentage of the unemployed Nigerian youth at 2020) in its estimate as shown below (35, 37). The sample size of 235 was calculated at a 95% confidence level and a margin error of 5% using an online calculator (40). Using a 10% expected dropout. The sample size is approximately 260 (130 per group). The formula used is shown below:

$$n=\frac{z^{2}\times \hat{p}(1-\hat{p})}{\varepsilon^{2}}$$

Where:

n is the sample size

z score (1.96 for 95% confidence level)

ε is the margin of error (0.05)

p̂  is the population proportion (0.188)

Study participants will be selected using a multi-stage sampling technique, that will incorporate non-randomized, purposive sampling technique at the state, within the state, schools/community, and individual levels. The details below describe how the estimated sample size will be achieved with the sampling technique.

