While the study involves self-reported outcomes and other measures, enumerators will be trained before the data collection period to uphold participant confidentiality to encourage honest responses and reduce response bias. To further minimize response bias in self-reported data, confidentiality assurances will be emphasized during the consent process. Moreover, the proposed analysis, mixed method, will control confounding factors to minimize the differences in participants’ characteristics and account for variability in the data. Additionally, participant dropout is anticipated; however, oversampling will address attrition, and the mixed model analysis will address missing data. The context-specific approach serves to enhance the relevance of an intervention and its applicability in a given study setting the generalizability may be limited for those regions with totally different infrastructures or sociocultural contexts. Nevertheless, the knowledge acquired provides a valuable learning base for designing comparable interventions in other contexts, still through appropriate contextual adaptations. The study is designed to assess the immediate impact of the intervention on nutritional knowledge, dietary habits, and participation in agricultural activities. The longer-term effects of the intervention, particularly about sustainable nutritional changes and health indicators, will be better understood through future longitudinal or follow-up studies. Future studies should put the study findings into perspective and further clarify the effectiveness of the interventions over time.

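### The complete-case analysis named as the check for missing-data bias cannot show that the mixed-model results are robust to outcome-related dropout

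*Protocol article*

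**What the plan says.** Section 2.5 (Data analysis) sets the check and its purpose in one sentence: to see whether missing values may have caused bias, "we will conduct sensitivity analyses by carrying out complete case analyses". The next sentence says what it will achieve: "this will ensure the robustness and credibility of our result". The reference cited for that assurance is the one the following paragraph cites for thematic analysis of the qualitative data.

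The same section explains the main analysis: "The mixed model analysis was chosen because it accounts for repeated measures and can effectively address issues related to missing data". The mixed model, with arm, time and their interaction, is named for skin carotenoids, anthropometrics and dietary diversity. Section 3.1 returns to dropout: "oversampling will address attrition, and the mixed model analysis will address missing data".

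Section 2.2.1 anticipates 10% dropout and arrives at about 260 participants, 130 per group. Section 2.4 and Table 2 show that these outcomes are measured twice, at baseline and post-intervention. The article names no other missing-data check and does not state the missingness assumption behind the mixed model.

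**The concern.** A likelihood-based mixed model is valid if data are missing at random, that is, if participants without a post-intervention value resemble those with the same observed data who have one. Comparison with completers does not test this. With two waves, someone who lacks the post value contributes only a baseline to the mixed model and nothing to the complete-case analysis. The two estimates are therefore nearly the same quantity computed from nearly the same data.

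At stake is what may be claimed. The plan commits in advance to reading the complete-case result as proof of robustness. If dropout depended on the outcome and differed between arms, both estimates could be off in the same direction while appearing to support each other. Section 3.1 itself concedes that interest in gardening may fade, and only one arm has ten weeks of WhatsApp tasks, so engagement-related dropout is possible. Oversampling restores numbers but does not remove bias.

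**Working it through.** **The plan's own figure.** n = 1.96² × 0.188 × 0.812 / 0.05² = 234.6, rounded up to 235. For 10% dropout, 235 / 0.90 = 261.1 and 235 × 1.10 = 258.5; the stated 260 lies between them. The missing-data statement itself rests on no figure.

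**Inputs from the article.** 130 per arm, 10% dropout, two waves, arm-by-time contrast.

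**Assumptions not in the article.** Outcome in SD units; baseline–post correlation 0.5 (range 0.3 to 0.7); logistic dropout in which low post-intervention values are more likely to be missing, log-odds 1 per SD (range 0.5 to 2); no covariates.

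**Standard error of the contrast.** The variance of change is 2 × (1 − 0.5) = 1. With 130 × 0.90 = 117 per arm, SE = √(2 × 1 / 117) = 0.131 SD.

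**Large-sample bias when dropout depends on the post value** (WhatsApp arm v gardening-only arm; the signs reverse if the split reverses):

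| Dropout | Mixed model | Complete case | Gap | Mixed-model bias / SE |
|---|---|---|---|---|
| 10% v 10%, same mechanism | 0.00 | 0.00 | 0.00 | 0 |
| 12% v 8% | +0.025 | +0.017 | about 0.01 | 0.2 |
| 15% v 5% | +0.066 | +0.043 | 0.023 | 0.5 |
| 20% v 5% | +0.098 | +0.063 | 0.035 | 0.75 |

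At 15% v 5%, the mixed-model bias runs from about 0.08 to 0.05 as the correlation goes from 0.3 to 0.7, and from 0.036 to about 0.10 as the log-odds slope goes from 0.5 to 2.

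**Different assumptions, not a hierarchy** (15% v 5%, correlation 0.5, slope 1):

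| Dropout depends on | Mixed model | Complete case |
|---|---|---|
| Post value | +0.066 | +0.043 |
| Observed baseline | 0.00 | −0.043 |
| Stable personal trait | +0.032 | 0.00 |

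**Does the gap separate safe from unsafe?** In simulated trials of 130 per arm with 10% dropout in each and correlation 0.5, the mean absolute difference between the two estimates was:

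- 0.016 SD when dropout was completely random (no bias in either);
- 0.025 SD when it depended on the post value in the education arm only (mixed model +0.063, complete case +0.040);
- 0.046 SD when it depended on baseline in that arm only (mixed model unbiased, complete case −0.048).

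The two estimates correlated 0.98 to 0.99. The largest gap arose where the mixed model was sound.

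**What a delta shift shows.** If a fraction m of one arm is missing and those values are shifted by d SD, the contrast moves by m × d: 0.10 × 0.5 = 0.05 SD, and 0.20 × 0.5 = 0.10 SD. Complete-case analysis gives no such range.

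**The case against.** Several things can be said for the plan.

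- **Complete-case analysis is not simply the weaker method.** This stands. If dropout follows a stable trait, the completer change contrast is unbiased and the mixed model is not. A reader might infer that complete-case analysis always needs the stronger assumption, but the second table shows otherwise.
- **The size depends on invented inputs.** This also stands. The article gives 10% dropout and no split by arm. With the same mechanism and rate in both arms the bias is about 0, and the covariates in the adjusted models could reduce it elsewhere.
- **The direction is unknown.** A reader might infer that the bias would favour the WhatsApp arm because of its extra tasks. The documents do not support that. Those participants are chosen for phone access and digital literacy, which may help retention, and outcomes come from enumerator-administered surveys, separate from WhatsApp activity. Eligibility requires another year of enrolment or residence.
- **Agreement is not certain.** With 30% dropout and opposite mechanisms in the arms, the mean gap reached 0.134 SD, about one standard error (0.142 SD).
- **Further sensitivity analyses belong in a statistical analysis plan.** That would excuse silence. Here the article names the check, states its purpose and declares what it will prove.

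None of these points makes complete-case analysis able to do the job assigned to it.

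**Conclusion.** The point holds in a limited form. The complete-case analysis is the article's only check on missing-data bias, and its result cannot bear the claim attached to it in either direction.

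The possible bias is modest near the planned dropout: nil with equal dropout by the same mechanism, about 0.2 SE at 12% v 8%, and 0.5 to 0.75 SE at 15% v 5% or 20% v 5%. Equal rates alone do not guarantee safety, since 10% in each arm with outcome-related dropout in one arm only gave +0.063 SD. All these sizes rest on the assumed correlation, slope and dropout pattern.

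The comparison concerns only skin carotenoids, anthropometrics and dietary diversity. For the other primary outcomes the article names no mixed model to compare with. Nothing here shows that the mixed model will be biased; it shows that the planned check could not tell.

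**What to change.** In Section 2.5, for skin carotenoids, anthropometrics and dietary diversity:

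1. State that the mixed model assumes data are missing at random.
2. Report dropout, and the baseline characteristics of those who drop out, by arm.
3. Add a delta-adjusted (tipping-point) sensitivity analysis: impute missing post-intervention values under the mixed model, shift them separately by arm in both directions (for example −0.5 to +0.5 SD), and report the shift at which the arm-by-time conclusion changes. Both directions are needed because BMI has no single adverse direction and the arm losing more participants is not known.
4. Keep complete-case results as supplementary description, and remove the statement that they ensure robustness. Section 3.1 should be worded to match.

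The cost is a few sentences and a little more analysis work, with no new data or participants.
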